## Abstract

**Background:**

Ankylosing spondylitis (AS), a chronic inflammatory disease, causes spinal stiffness, functional impairment, and reduced quality of life. While exercise is critical for managing AS, traditional home-based programs lack real-time supervision to ensure movement quality and adherence. Emerging digital tools like inertial sensors may address this gap, but their clinical impact remains unproven.

**Objective:**

This study aims to evaluate the feasibility and efficacy of a Digital Functional Exercise Program (DFEP) using wearable sensors and real-time feedback for patients with AS.

**Methods:**

This single-blind randomized controlled trial (ChiCTR2300068327) enrolled 80 adults with AS from the Chinese People’s Liberation Army (PLA) General Hospital. Participants were randomized 1:1 to: DFEP Group: 24-week sensor-guided exercises via the Healbone Mini Program (Jiakangzhongzhi, Co), with real-time feedback and remote physiotherapist oversight. Control Group: standard home-based exercises with written instructions. The primary outcome is the change in Ankylosing Spondylitis Disease Activity Score with C-reactive protein (ASDAS-CRP) at 24 weeks. Secondary outcomes include Bath Ankylosing Spondylitis Disease Activity Index (BASDAI), Bath Ankylosing Spondylitis Functional Index (BASFI), Bath Ankylosing Spondylitis Metrology Index (BASMI), Assessment of Spondyloarthritis International Society Health Index (ASAS HI), 36-Item Short Form Survey (SF-36), pain visual analog scale, Five-Times-Sit-to-Stand, 4-meter walk test, Hamilton Anxiety Scale (HAMA), Hamilton Depression Scale (HAMD), and adherence. Analyses will follow an intention-to-treat approach with the Last Observation Carried Forward for missing data; continuous variables will be compared with *t* tests or ANOVA, and categorical variables with chi-square tests, using a 2-sided =.05.

**Results:**

We have screened 216 outpatients who may be eligible subjects, among them 126 outpatients who initially met the inclusion criteria. After evaluating clinicians performed face-to-face assessments, 23 lacked a stable medication regimen, 5 presented with severe cervical vertebral bridges, 3 reported regular structured exercise, 2 could not be reached after prescreening, 10 had significant cardiovascular disease, and 3 declined participation due to time constraints. Ultimately, 80 eligible participants were enrolled, with 36 randomly allocated to the intervention group and 44 to the control group. Recruitment (February 2023-March 2024) and follow-up (concluding September 2024) are complete. Data analysis (November 2024) and result dissemination (April 2025) are pending.

**Conclusions:**

This trial is the first to test a fully digital, sensor-based exercise program for AS. If effective, DFEP could offer a scalable, cost-effective solution for home rehabilitation in AS and related conditions.

**Trial Registration:**

Chinese Clinical Trial Registry ChiCTR2300068327; https://www.chictr.org.cn/showproj.html?proj=190897

**International Registered Report Identifier (IRRID):**

DERR1-10.2196/67556

## Introduction

Ankylosing spondylitis (AS) is a chronic, systemic rheumatic disease that serves as the prototype of spondyloarthritis and is primarily characterized by inflammation of the spine [1]. The principal clinical features of AS include reduced physical activity, pain, stiffness, sleep disturbances, decreased spinal mobility, and psychological consequences such as depression [2]. Less frequently, AS affects peripheral joints and causes extra-articular manifestations, such as Achilles tendinitis, uveitis, psoriasis, and inflammatory bowel disease.

The main objectives of treatment are to alleviate symptoms, improve functioning, maintain the ability to work, decrease disease complications, and minimize skeletal damage. However, pharmacological therapy alone is often insufficient in managing AS, especially in patients with existing functional limitations. The importance of exercise in AS has been emphasized in the Assessment of SpondyloArthritis international Society/European League Against Rheumatism (ASAS/EULAR) recommendations for the management of AS [3]. Although there is no clear consensus on which specific exercise is the most effective, a comprehensive functional exercise program including stretching, mobilization, strengthening, and balance exercise is recommended.

A recent meta-analysis found that both supervised and home-based exercise programs are beneficial in reducing Bath Ankylosing Spondylitis Metrology Index (BASMI), Bath Ankylosing Spondylitis Disease Activity Index (BASDAI), and Bath Ankylosing Spondylitis Functional Index (BASFI) in patients with AS, with supervised exercise programs showing greater efficacy than home-based exercise programs in decreasing disease activity [4]. The main reason for this result is that supervised exercise could improve the compliance of patients with exercise, improve the accuracy of exercise, leading to better therapeutic outcomes. Fortunately, the development of electronic medicine is being driven by mobile technologies, including smartphones and other wireless communication devices [5]. In recent years, mobile devices have experienced dramatic innovations, enabling anytime, anywhere, and real-time connectivity and interactions. Unlike single physiological indicators such as heart rate, functional exercise involves complex multijoint movements, dynamic ranges of motion, and postural corrections. Traditional home-based exercise models lack real-time feedback, making it challenging to simultaneously evaluate movement accuracy, adherence, and clinical progress. While digital health technologies have advanced significantly, few studies have rigorously tested scalable solutions that merge the flexibility of home-based routines with the precision of supervised guidance—a critical gap hindering the development of accessible, long-term management strategies for AS. Building on our prior work with a WeChat mini-program to monitor home-based functional exercises in patients with AS [6], we have now integrated inertial sensors into an upgraded WeChat applet. This innovation enables real-time tracking of movement quality and adherence, addressing the limitations of traditional models by providing objective, quantifiable feedback akin to in-person supervision.

This randomized controlled trial aims to evaluate the feasibility and efficacy of a digital functional exercise program for patients with AS. We hypothesize that the intervention group using the digital platform (Healbone) will demonstrate superior improvements in disease activity, measured by the Ankylosing Spondylitis Disease Activity Score with C-reactive protein (ASDAS-CRP), compared to the control group receiving standard home-based exercises. Secondary hypotheses posit greater enhancements in physical function (BASFI), spinal mobility (BASMI), and quality of life (36-Item Short Form Survey [SF-36]) in the intervention group, attributable to improved exercise adherence and real-time feedback mechanisms.

## Methods

### Study Design

This randomized, prospective, controlled study was a single-blind trial, conducted at the Department of Rheumatology and Immunology, Chinese People’s Liberation Army (PLA) General Hospital. After baseline assessments by an assessor who was blinded to the group assignments, eligible participants were randomly assigned to the trial group or the control group after providing informed consent. Assessors were blinded to group allocation, but participants were aware of their assigned intervention (digital platform or manual-based exercise) due to the inherent nature of the interventions. This pragmatic design reflects real-world conditions where patients would typically know their treatment modality. This protocol is in line with CONSORT (Consolidated Standards of Reporting Trials) guidelines (checklist in Multimedia Appendix 1).

### Participants

Patients diagnosed with AS according to the 1984 modified New York criteria [7] at the Chinese PLA General Hospital, either as a first-time diagnosis or previously, were enrolled in the study and assigned to 2 groups. In addition to collecting their demographic characteristics (age, gender, weight, height, and BMI), the patients were also questioned about occupation, main symptoms, time of diagnosis, and drug usage (nonsteroidal anti-inflammatory drug, disease-modifying antirheumatic drugs, including biologics). Other inclusion criteria were aged ≥18 years, stable drug treatment in the preceding month, and ASDAS-CRP between 1.3 and 3.5 [8]. Exclusion criteria were cardiovascular disease or clinical status at high risk, screened with the American Heart Association/ACSM Health/Fitness Facility Preparticipation Screening Questionnaire [9], cervical vertebra bridges, surgery within the preceding 6 months, regular exercise in the preceding 3 months (eg, yoga, Tai Chi, Baduanjin 3 or more times per week, 20 minutes per time), and factors leading to the inability to receive regular exercise rehabilitation (such as language impairment, difficulty in understanding, and limited movements).

### Procedures

All subjects in this study were patients diagnosed with AS in the outpatient Department of Rheumatology and Immunology, in the Chinese PLA General Hospital. First, the potentially eligible subjects were screened by a study physician, and the exclusion criteria of all screened patients were recorded. Then, the informed consent form was signed for eligible subjects, and the baseline data were collected in detail. The trial implemented evaluation physician blinding at both baseline and follow-up phases, with group allocation data concealed via an opaque envelope. Postassessment allocation to a physical therapist for exercise prescription occurred through a separate workflow managed by the trial coordinator. Finally, a personalized exercise rehabilitation scheme was given to all the subjects by the physical therapist according to the patient’s function evaluation (Multimedia Appendix 2).

### Interventions

A 24-week tailored functional exercise program, consisting of stretching, mobilization, and strengthening exercises, was designed based on the patients’ basic functional abilities following randomization. All patients had a 1-hour training session at entry, providing information about AS and the purpose of physical exercises.

In addition to a face-to-face session, participants in the experimental group received a digital exercise program given by the physiotherapist. Participants in the intervention group were taught the usage of the digital exercise project that will be delivered via WeChat applets to individual exercise interfaces. In the first step, patients needed to wear a sensor on their chest, close to their armpits, and then connect to their mobile phones via Bluetooth. After a successful connection, they carried out the personalized workout program listed in Multimedia Appendix 2. During exercise, participants in the experimental group received real-time feedback on movement standardization and joint angles via the WeChat-based exercise applets. Postexercise feedback was systematically collected using the Borg Rating of Perceived Exertion scale (Figure 1), enabling adjustments to exercise regimens based on participants’ subjective experiences of effort.

**Figure 1 figure1:**
[figure not shown]
Schematic representation of training feedback.

The physiotherapist’s management platform enabled remote monitoring of participants’ home exercise compliance through real-time data transmission from wearable sensors. Participants were instructed to complete exercises 3-4 times per week, with session frequency and duration tailored to their baseline functional assessments. To reinforce adherence, automated reminders were triggered via the platform if a participant missed exercise sessions for 7 consecutive days, prompting re-engagement through personalized notifications (eg, motivational messages and corrective feedback). Physiotherapists reviewed compliance metrics weekly to adjust exercise prescriptions or provide additional guidance as needed.

The participants in the control group received a home-based exercise program, and an exercise manual was given to each participant. The participants in the control group were also recommended to perform the exercise 3-4 times per week. Participants in the control group were provided with a paper logbook to record exercise frequency, duration, and perceived exertion. Research assistants conducted biweekly phone follow-ups to collect logbook data, reinforce adherence, and address participant questions. Adherence was calculated as the self-reported ratio of completed sessions to prescribed sessions (3-4 sessions/wk), mirroring the intervention group’s digitally recorded adherence metric.

To minimize deviation risks, we established WeChat patient management groups for each participant (both control and intervention groups) comprising: the enrolled patient, a rheumatologist, a physical therapist, and a digital health assistant. The physical therapist provided targeted assistance in the intervention group under two predefined conditions: (1) when abnormal exercise difficulty was detected through our background monitoring system, and (2) if the intervention group participants failed to complete exercises consecutively for 1 week.

For participants in the control group, physical therapists solely addressed inquiries related to medical conditions and exercise clarification, without providing proactive rehabilitation guidance or progress monitoring. All communication occurred digitally via the WeChat platform except during scheduled in-person outpatient follow-up visit. No additional face-to-face meetings were conducted beyond these standard clinical appointments.

### The Digital Platform

The digital exercise platform, Healbone, was developed through a participatory design process involving patients with AS and their relatives, rheumatology specialists, physical therapists, and a technical team. Healbone serves as a shared communication platform accessible to patients, their families, and associated health care professionals. Patients must provide written consent regarding data sharing. All information is uniformly available to all participants. Health care personnel and researchers have access to additional tools for managing care, obtaining overviews of patient conditions, and simultaneously monitoring multiple patients. The platform also functions as a coordination and communication tool among patients, relatives, and health care professionals.

All measurements are securely stored in a database. The web-based Healbone platform includes multiple features designed and developed through user-driven innovation. Facilities and input data specific to individual patients, such as symptom scores, are accessible and available to authorized personnel. The main features include:

Video consultation: Patients can conduct video calls with the health care team to receive professional advice and support.Messaging: The platform facilitates message exchange between patients and doctors, enhancing communication and follow-up.Personalized exercise plans: Tailored exercise plans are generated based on the patient's specific condition, with daily reminders.Exercise tracking: Real-time monitoring and recording of patients' exercise activities.Educational resources: The platform provides educational materials on AS management and exercise, aiding patients in better understanding and managing their condition.Calendar: Patients can record appointments and other activities with the health care team for easy viewing.Status tracking: Overview of questionnaire results completed by patients, available for viewing by patients and their authorized relatives and health care professionals.To ensure the security of patient data, Healbone uses the following measures: (1) data encryption: all data are encrypted during transmission and storage; (2) user authentication: two-factor authentication ensures that only authorized users can access the platform; and (3) privacy policy: The platform complies with General Data Protection Regulation (GDPR) and other relevant data privacy regulations to protect user privacy.

In addition, Healbone can integrate with electronic health record systems and other medical devices, enabling comprehensive data management and analysis to provide holistic health management support for patients. Through these features, the platform not only improves patients’ physical abilities and quality of life but also equips clinicians with effective tools for enhanced monitoring and treatment plan adjustments (Figure 2).

**Figure 2 figure2:**
[figure not shown]
The overview diagram of the Healbone digital platform.

**Figure 3 figure3:**
[figure not shown]
Treatment assignments and withdrawal in the participants. ITT: intention-to-treat.

### Randomization Scheme

All patients were recruited by a physician and randomly assigned to either the intervention or control group in a 1:1 ratio. To ensure allocation concealment, a computer-generated randomized table of numbers was prepared by an independent individual before the study’s commencement. The numbered cards indicating the random assignment and group allocation details were sealed in opaque envelopes by the same independent person. The physical therapist then opened these envelopes and administered the exercise program based on the assigned group.

### Assessments

For a schedule of data collection and measures list, refer to Table 1.

**Table 1 table1:** Measures and schedule for data collection.

Measure name			Screener		Baseline		24-week follow-up
**Demographics information**							
	Age	✓					
	Gender	✓					
	Weight	✓					
	Height	✓					
	Marital status	✓					
	Alcohol consumption	✓					
	Duration of smoking (years)	✓					
	Occupation	✓					
	HLA-B27^a^	✓					
	ESR^b^	✓				✓	
**Past history or symptoms at onset**							
	Psoriasis	✓					
	IBD^c^	✓					
	Uveitis	✓					
	Hypertension	✓					
	Hip pain	✓					
	Low back pain	✓					
	Neck pain	✓					
	Upper back pain	✓					
	Hip joint pain	✓					
	Other joint pain	✓					
	Disease duration (months)	✓					
**Family history**							
	Hypertension	✓					
	Diabetes	✓					
	AS^d^	✓					
**Physical examination**							
	Heel pain	✓		✓		✓	
	Joint pain	✓		✓		✓	
	Anterior chest pain	✓		✓		✓	
	Sacroiliac joint pain	✓		✓		✓	
	Hip pain	✓		✓		✓	
	Chest expansion			✓		✓	
	Finger-to-floor distance			✓		✓	
	Five Times Sit to Stand Test			✓		✓	
	4-meter walk test			✓		✓	
	ASDAS-CRP^e^			✓		✓	
	ASAS HI^f^			✓		✓	
	BASDAI^g^			✓		✓	
	BASFI^h^			✓		✓	
	BASMI^i^			✓		✓	
	MASES^j^			✓		✓	
	HAMA-14^k^			✓		✓	
	HAMD-17^l^			✓		✓	
	VAS^m^ night pain			✓		✓	
	VAS 24-h pain			✓		✓	
	PGA^n^			✓		✓	
	PhGA^o^			✓		✓	
**SF-36^p^**							
	Physical function			✓		✓	
	Physiological role			✓		✓	
	Bodily pain			✓		✓	
	General health			✓		✓	
	Vitality			✓		✓	
	Social functioning			✓		✓	
	Emotional role			✓		✓	
	Mental health			✓		✓	
	Overall health			✓		✓	
	Adherence					✓	

^a^HLA-B27: human leukocyte antigen B27.

^b^CRP: C-reactive protein.

^c^IBD: inflammatory bowel disease.

^d^AS: ankylosing spondylitis.

^e^ASDAS-CRP: Ankylosing Spondylitis Disease Activity Score with C-reactive protein.

^f^ASAS HI: Assessment of Spondyloarthritis International Society Health Index.

^g^BASDAI: Bath Ankylosing Spondylitis Disease Activity Index.

^h^BASFI: Bath Ankylosing Spondylitis Functional Index.

^i^BASMI: Bath Ankylosing Spondylitis Metrology Index.

^j^MASES: Bath Ankylosing Spondylitis Functional Index.

^k^HAMD-17: 17-item Hamilton Depression Scale.

^l^HAMA-14: the 14-item Hamilton Anxiety Scale.

^m^VAS: visual analog scale.

^n^PGA: patient global assessment.

^o^PhGA: physician global assessment.

^p^SF-36: 36-Item Short Form Survey.

#### Primary Outcome

ASDAS, including total back pain, patient global assessment of disease activity, peripheral pain or swelling, duration of morning stiffness, and C-reactive protein level, is the primary outcome [10].

#### Secondary Outcomes

BASDAI, BASFI, and BASMI [11], which are used to reflect disease activity, will also be evaluated.

Assessment using the Spondyloarthritis International Society Health Index (ASAS HI) is performed to determine the common difficulties of patients with AS [12]. In addition, health-related quality of life is measured using the SF-36, including physical function; role of physical, bodily pain, general health, vitality, social functioning; and role of emotional, and mental health [13].

Hamilton Depression Scale (HAMD) is performed before and after the intervention. It is summarized into seven types of factor structures: (1) anxiety or somatization: mental anxiety, physical anxiety, gastrointestinal symptoms, hypochondriasis, and insight; (2) weight: weight loss; (3) cognitive disorders: guilt, suicide, agitation, depersonalization and derealization, paranoid symptoms, and obsessive‐compulsive symptoms; (4) day and night changes; (5) block: depression, work and interest, block and sexual symptoms; (6) sleep disorder: difficulty falling asleep, lack of sleep and early awakening; and (7) feeling of despair: feeling of loss, hopelessness and low self‐esteem. Scores of <8 points or less: no depression; 8 to <20 points: prone to depression; 20 to <35 points: depression; ≥35 points: severe depression.

Hamilton Anxiety Scale (HAMA) is performed before and after the intervention. Score interpretation is as follows: ≤7 points indicate no clinically significant anxiety; 8-14 points suggest possible (mild) anxiety; 15-21 points reflect moderate anxiety; and ≥ 22 points indicate severe anxiety.

Exercise adherence is defined as the ratio of the actual completed amount of exercise (recorded via the Healbone platform) to the recommended amount (3-4 sessions/wk), which will be quantified and compared between groups.

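### The depression outcome is labelled the 17-item Hamilton scale, but the scoring text names 23 items, so either the label or the scoring rule is wrong

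*Protocol article*

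**What the plan says.** The schedule in Table 1 lists HAMD-17 at baseline and at 24 weeks, and the footnote expands it as "HAMD-17: 17-item Hamilton Depression Scale". The Abstract names the Hamilton Depression Scale among the secondary outcomes.

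The Secondary Outcomes section gives no item count for the scale. It says "It is summarized into seven types of factor structures" and then names the items under each factor. The same paragraph ends with the severity bands: a lowest band for no depression, followed by "8 to <20 points: prone to depression; 20 to <35 points: depression; ≥35 points: severe depression". The lowest band is worded with both a less-than sign at 8 and an or-less phrase, while the next band starts at 8.

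The Statistical Analyses section assigns t tests or one-way ANOVA to quantitative variables and chi-square tests to categorical ones. It does not say which of these applies to the depression scale.

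**The concern.** A scale has one item set, and its factor structure and cut-offs belong to that set. Here the schedule states one length and the scoring paragraph lists more items than that length allows. Someone programming the outcome from the article could not follow both.

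The stakes differ with the version actually used:

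- **17-item form administered.** Some listed items do not exist in the data, so the factor scores cannot all be built as described. The only bands the article offers sit beside a longer list and may not suit a 17-item total.
- **Longer form administered.** The scoring text may be sound, but readers would take the reported means and SDs as 17-item totals and judge them against the wrong range.

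**Working it through.** **Inputs.** The labelled length is 17 items (Table 1 and its footnote). The items are counted from the seven factors in Secondary Outcomes:

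1. Anxiety or somatization: "mental anxiety, physical anxiety, gastrointestinal symptoms, hypochondriasis, and insight" gives 5.
2. Weight: "2) weight: weight loss" gives 1.
3. Cognitive: "guilt, suicide, agitation, depersonalization and derealization, paranoid symptoms" gives 5, and the obsessive-compulsive item that follows makes 6.
4. Diurnal variation: "4) day and night changes" gives 1.
5. Block: "5) block: depression, work and interest, block and sexual symptoms" gives 4.
6. Sleep: falling asleep, insufficient sleep and early waking give 3.
7. Despair: loss, hopelessness and low self-esteem give 3.

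**Count.** 5 + 1 + 6 + 1 + 4 + 3 + 3 = 23.

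**Other readings.** If block and sexual symptoms are one item, 23 − 1 = 22. If depersonalization and derealization are two items, 23 + 1 = 24. The excess over the label is 23 − 17 = 6, with a range of 22 − 17 = 5 to 24 − 17 = 7. The stated length of 17 is not reproduced under any of these readings.

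**Direction of a possible misclassification (illustration only).** The article gives no item score range, no maximum total and no bands specific to a version. Assume that the 17-item form was used, that the bands belong to the listed items, and that totals scale with the number of items. Then each cut-off c corresponds to c × 17/23 on the short form:

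- 8 × 17/23 = 5.9 (5.7 with 24 items, 6.2 with 22)
- 20 × 17/23 = 14.8 (14.2 to 15.5)
- 35 × 17/23 = 25.9 (24.8 to 27.0)

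Put another way, reaching 35 needs a mean item score of 35/17 = 2.06 on 17 items, against 35/23 = 1.52 on 23. Bands applied unchanged would then place patients too low. The third assumption has no support in the article, so these figures show direction, not size.

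**What does not move.** The Power Calculations section uses ASDAS-CRP with an effect size of 0.714. The exact two-sided t test gives power 0.803 at 32 per group, and 64/(1 − 0.20) = 80, so the stated sample size reproduces and has no link to this scale.

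**The case against.** The strongest reply is that nothing computed need be wrong. If the longer form was given, and the list and bands belong to it, the categories are correct and only a table label is at fault. That is plausible: the footnotes to Table 1 contain other slips. The ESR row carries a marker defined as CRP, MASES is expanded as the BASFI, and the markers for the two Hamilton scales are swapped between rows and footnotes. This argument stands as far as it goes. It does not prove a labelling slip, because the 17-item name appears in both the row and the footnote. Even on this reading, the schedule of a named outcome is wrong.

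A reader might infer that a chi-square test on depression category would be wrong whichever form was used. The article does not support this. It specifies no test of depression category and no analysis of factor scores; the bands are given as interpretation, as they are for the anxiety scale. With the longer form, the categories may well be right.

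A reader might also infer that the bands are certainly wrong for a 17-item total. That the bands belong to the longer list is an inference from their position in the paragraph, since no version is stated.

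The overlap at 8 is a matter of wording. The second band explicitly starts at 8, so the intended boundary can be recovered.

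**Conclusion.** The contradiction stands on the article alone: a scale labelled as 17 items is scored from a list of 23 (22 to 24). The label or the scoring text is wrong, and the article does not show which.

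The consequences are conditional. The factor-score problem needs the 17-item form to have been used. The downward misclassification needs that and also that the bands belong to the longer list; its size cannot be fixed from the article. If the longer form was used, the damage is a wrong instrument name and totals read against the wrong range.

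A between-arm comparison of mean totals does not use the bands, although its interpretation in points depends on the version. The primary outcome and the sample size are untouched. The text is wrong as written, but the point is minor and confined to one secondary outcome.

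**What to change.** Before analysis:

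1. Confirm from the case report form which version was administered.
2. Make the Table 1 label, the factor list and the severity bands agree with that version, and correct the swapped footnote markers for the two Hamilton scales at the same time.
3. Reword the lowest band so that it does not overlap the band starting at 8.
4. Analyse the total score as continuous, adjusted for its baseline value. The contradiction can be resolved without this step, but it is a free gain over the stated t test because the baseline score is already collected.
5. Report severity bands or factor scores only with definitions that match the version used.

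The cost is a check of the form and a text correction. The article describes data analysis as pending, and no new data are needed.

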### Limitations

This study has several limitations. One is that the patients are recruited for PLA General Hospital, which may limit the generalizability of the results to the rest of China and internationally. However, patients come from across the country, accordingly reducing some regional differences. Second, the differing monitoring strategies between groups-digital tracking for the intervention group versus self-reporting for the control group—may influence adherence comparisons. While this reflects real-world disparities between standard and technology-enhanced care, it introduces potential measurement bias. Future studies could use matched monitoring methods (eg, wearable devices for both groups) to isolate the effect of the digital platform itself, independent of adherence measurement tools. Finally, the exclusion of regularly active individuals may reduce the generalizability of our results. However, this approach aligns with prior trials aiming to evaluate novel interventions in controlled settings.

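### Adherence is defined by platform records and compared between arms, but controls self-report in logbooks, so instrument is confounded with arm and the P value is not a test of adherence

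*Protocol article*

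**What the plan says.** Adherence is a listed secondary outcome. The Secondary Outcomes section gives it one definition for the whole trial, a ratio: "actual completed amount of exercise (recorded via the Healbone platform) to the recommended amount (3-4 sessions/wk), which will be quantified and compared between groups". The Statistical Analyses section assigns quantitative variables a t test or one-way ANOVA, with significance at P<.05.

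The Interventions section describes two different recording systems. In the intervention (DFEP) arm, sensor data reach the physiotherapist's platform. For the other arm: "Participants in the control group were provided with a paper logbook to record exercise frequency, duration, and perceived exertion". Research assistants telephone every two weeks to collect the logbook data, and the same call is meant to reinforce adherence. The control formula follows: "Adherence was calculated as the self-reported ratio of completed sessions to prescribed sessions (3-4 sessions/wk"). The article describes this as mirroring the digital metric.

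The Introduction expects the secondary benefits to be "attributable to improved exercise adherence and real-time feedback mechanisms". Principal Findings in the Discussion likewise expects benefit to come from higher adherence in the intervention group. Limitations acknowledges the different monitoring and says "it introduces potential measurement bias". It leaves matched monitoring to future studies.

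**The concern.** As written, the outcome definition cannot be computed for 44 of the 80 participants, because they have no platform record. Applying the control formula from Interventions fills the gap with a different instrument. Nobody is described as being measured both ways, so the size of the instrument difference cannot be estimated within the trial.

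The direction of the error is also open. Controls may over-report to a caller who is encouraging them, and the platform may miss sessions when the sensor does not connect. Either would understate a true advantage for the intervention. Incomplete logbooks would overstate it. A significant, null or reversed result would each have a measurement explanation beside the behavioural one. The adherence explanation in the Introduction and Discussion would lean on this comparison.

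**Working it through.** **The plan's own figure.** The article gives no numerical assumption for adherence. Its only calculation is for ASDAS-CRP, and it reproduces: with effect size 0.714 and two-sided α = .05, exact t-test power is 0.790 at 31 per group and 0.803 at 32, so 32 per group (64 in total), and 64 / 0.8 = 80. This does not bear on the adherence comparison.

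**What the comparison estimates.** Let Δ be the true difference in mean adherence, and b the difference between arms in mean measurement error. The observed difference has expectation Δ + b. With platform records only in one arm and logbooks only in the other, b cannot be separated from Δ.

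**Illustrative size.**
- From the article: n₁ = 36 and n₂ = 44 (Results); t test at P<.05 (Statistical Analyses), taken as two-sided as in the Abstract.
- Assumed, because the article gives neither: |b| of 5 or 10 percentage points; SD of 15, 25 or 30 points.
- Formula: noncentrality λ = (|Δ + b| / SD) × √(n₁n₂ / (n₁ + n₂)), with n₁ + n₂ − 2 = 78 degrees of freedom.
- √(36 × 44 / 80) = √19.8 = 4.45.

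With no true difference (Δ = 0):

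| Assumed bias | SD 15 | SD 25 | SD 30 |
|---|---|---|---|
| 5 points | 0.31 | 0.14 | 0.11 |
| 10 points | 0.83 | 0.42 | 0.31 |

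Entries are the probability that the test rejects; the nominal value is 0.05. For example, a bias of 10 with SD 25 gives λ = 0.40 × 4.45 = 1.78 and probability 0.42. The sign of b decides which arm appears better.

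With a true 15-point advantage for the intervention and SD 25, λ = 0.60 × 4.45 = 2.67 and power is 0.75. If controls over-report by 10 points, the expected observed difference is 15 − 10 = 5, λ = 0.20 × 4.45 = 0.89, and power falls to 0.14.

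**Denominator.** Both formulas carry a range. Over 24 weeks, 3 per week is 72 sessions and 4 per week is 96. A participant who completes 72 scores 72/72 = 100% or 72/96 = 75%. This is the extreme case. It disappears if each person has an individual target and that target is the denominator.

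**The case against.** The strongest defence is that the article is open about the problem. It states a control-arm formula, calls it a mirror of the digital one, and admits the bias. Adherence is secondary, no mediation analysis is described, and the randomized ASDAS-CRP comparison does not use it. All of that is true, and it limits the seriousness of the point. It does not repair the comparison: Limitations names the bias, while Secondary Outcomes keeps a definition that controls cannot meet.

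A reader might infer more than the text supports:

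- *The comparison measures only the instrument.* It does not. It mixes a real difference with an instrument difference.
- *It could never support the adherence explanation.* That depends on the direction of error. If error runs only against the intervention, higher recorded adherence there would still be supportive, though understated. The article does not establish the direction.
- *The two arms use different numerators.* The wording differs (amount of exercise against sessions), but the first is divided by sessions per week and reads naturally as sessions.
- *The intervention arm's denominator moves with compliance.* The article says "Physiotherapists reviewed compliance metrics weekly to adjust exercise prescriptions or provide additional guidance as needed", but not that the number of sessions changes.
- *The 3-4 range biases the comparison.* The same range is stated for both arms, individual prescriptions may resolve it, and a scoring rule can reasonably sit in the full protocol.

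Deleting the adherence hypothesis would also go too far. It is a stated prior hypothesis, and it names real-time feedback as a second mechanism.

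**Conclusion.** The point holds for one secondary outcome. Secondary Outcomes and Interventions conflict on how adherence is recorded, and recording method is fully confounded with arm. A P value from the planned test cannot be read as a test of adherence. The two-section mismatch and the confounding rest on the text alone. The 11% to 83% range is an illustration and depends wholly on the assumed bias and SD; it is not a prediction for this trial. The primary comparison stands.

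**What to change.** 1. In Secondary Outcomes, state both data sources, platform for the intervention arm and logbook for controls, and reconcile the definition with Interventions.
2. Use one numerator (sessions) and one denominator rule in both arms: each participant's prescribed sessions over 24 weeks, with a stated rule for scoring the 3-4 range and for any prescription that changed during follow-up.
3. Report adherence descriptively by arm, with a 95% confidence interval for the platform-recorded figure in the intervention arm. Label any between-arm difference as cross-instrument and do not test it at P<.05.
4. In the Introduction and in Principal Findings, keep the mechanism statements but add that this comparison cannot by itself establish that benefits arise from higher adherence.

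The cost is a between-arm P value for a listed secondary outcome. The Abstract reports follow-up as complete, so matched measurement can no longer be added, and the change alters a stated analysis after data collection. It should be reported as such, with the reason.
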